### Sample size calculation

There are no published seroprevalence studies exclusively for Cambodian children, but multiple pediatric seroprevalence studies are reported from neighboring Thailand and Malaysia [29–31]. The most recent incidence studies in Cambodia suggest that the most conservative estimate, or the lowest incidence rate, of acute dengue infection in Cambodia as approximately 14 per 1000 person-seasons (range 13.7–58 per 1000 person-seasons in neighboring province to Kampong Speu) [24].

It is difficult to make presumptions regarding the exposed mosquito saliva protein (MSP+) and unexposed mosquito saliva protein (MSP-) populations as the only available retrospective study data from Thailand suggested that seroconversion occurs to major *Ae. aegypti* proteins 0–25% of the time in non-infected hospitalized children *versus* 0–75% in DENV-infected hospitalized children [19]. Therefore, the sample size was primarily determined by the number necessary for DENV seroprevalence. With a sample size of 701 accounting for 10% dropout to yield a total goal enrollment of 771 participants, a simple random sample of a binary response (infected or not) with an exact 95% confidence interval on the true proportion will have an average length of less than or equal to 0.075 regardless of the true rate.

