## Methods/Design

### Study design and objectives

This is a prospective pagoda (community)-based cohort study with the following primary objectives: (i) to determine the seroprevalence of antibodies indicating previous *Aedes*-transmitted DENV infection in children; and (ii) to describe the seropositivity to *Aedes* salivary gland homogenate (Table 1). The study will screen up to 1200 and recruit up to 771 children aged 2–9 years for study enrollment and then follow them longitudinally for three years. The study is being conducted over three years given the high rate of variability in *Aedes*-transmitted disease transmission from year to year. The study is focused on children aged 2–9 years of age as they have the greatest burden of disease in Cambodia and thus offers comparability to other pediatric DENV cohorts [23–25, 27].

**Table 1 Tab1:** Study objectives and endpoints

Objectives	Endpoints	Justification for endpoints
• Primary		
Describe the seroprevalence of dengue infection (both symptomatic and inapparent) in children aged 2–9 years-old in Kampong Speu	Prevalence of symptomatic and inapparent dengue infection (serotypes 1–4) as detected semiannually *via* ELISA (binary outcome present/absent) over a 3-year period in Kampong Speu in children aged 2–9 years-old	Detailed knowledge of dengue seroprevalence and transmission season variability will help establish an epidemiological foundation to prepare for larger future studies such as disease incidence studies or vector interventional trials
Describe the seroprevalence of reactivity to *Ae. aegypti* salivary gland proteins in children aged 2–9 years-old in Kampong Speu	Prevalence of *Ae. aegypti* salivary gland homogenate reactivity as detected by ELISA assay (binary outcome present/absent) during wet and dry seasons over a 3-year period in Kampong Speu in children aged 2–9 years-old	Characterizing the *Ae. aegypti* salivary protein reactivity profile in Cambodians is the first step prior to assessing how *Ae. aegypti* saliva exposure modulates disease in humans
• Secondary		

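### The 10% dropout allowance multiplies 701 by 1.10, so 771 enrolled leaves about 694 evaluable children rather than 701; the loss of precision is minor

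*Protocol article*

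**What the plan says.** The Sample size calculation section bases the size of the cohort mainly on DENV seroprevalence, because too little is known about salivary seroconversion. It then states: "With a sample size of 701 accounting for 10% dropout to yield a total goal enrollment of 771 participants". The precision criterion is a simple random sample with a binary response, "with an exact 95% confidence interval on the true proportion", for which the interval "will have an average length of less than or equal to 0.075 regardless of the true rate". The construction of the exact interval is not named.

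The Study design and objectives section repeats the enrolment figure as a ceiling: "The study will screen up to 1200 and recruit up to 771 children aged 2–9 years". The primary endpoint is measured semiannually over three years (Table 1), and the Statistical analysis section reports seroprevalence as a proportion at each timepoint. Precision therefore depends on the number still measured at each visit.

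**The concern.** The dropout allowance is calculated on the wrong base. Dropout is a fraction of those enrolled, so the enrolment target should be the evaluable number divided by 0.90. The article's figure is the evaluable number multiplied by 1.10. Recruitment is capped at 771, so nothing in the plan makes up the difference.

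At stake is the only quantitative justification of the cohort size. If the planned 10% loss occurs, the follow-up visits have fewer children than the sentence assumes, and the interval length promised for any true rate has to be checked at that smaller number.

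**Working it through.** **Inputs, all from the Sample size calculation section:** evaluable n = 701; dropout 10%; enrolment 771; exact 95% interval, taken as two-sided; average length at most 0.075 at any true rate.

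**1. How 771 arises.** 701 × 1.10 = 771.1, which reproduces the stated 771.

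**2. What 771 delivers.**
- After a 10% loss: 771 × 0.90 = 693.9, about 694.
- Shortfall against 701: 7 children.
- Enrolment that keeps 701: 701/0.90 = 778.9, so 779, which is 8 more than 771 (8/771 = 1.0%).
- Largest loss at which 771 still leaves 701: 1 − 701/771 = 9.1%.

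**3. Precision under Clopper-Pearson.** Average length at true rate p is the sum over x = 0, …, n of Binomial(x; n, p) × (upper limit − lower limit at x). At these sample sizes it is largest at p = 0.5.

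| n | where it comes from | average length at p = 0.5 | true rates with length above 0.075 |
|---|---|---|---|
| 694 | 771 after 10% loss | 0.0757 | about 0.434 to 0.566 |
| 701 | stated evaluable number | 0.0753 | about 0.458 to 0.542 |
| 706 | smallest n at or below 0.075 | 0.0750 | none |
| 771 | all enrolled, baseline | 0.0717 | none |
| 779 | 701/0.90, all enrolled | 0.0713 | none |

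At n = 701 the length falls quickly away from p = 0.5: 0.0749 at p = 0.45, 0.0738 at 0.40, 0.0691 at 0.30 and 0.0605 at 0.20.

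**4. Other exact intervals.** Blaker's and the minimum-likelihood interval were obtained by inverting the test over a fine grid of p, then averaged as in step 3 at p = 0.5.

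| n | Blaker | minimum-likelihood |
|---|---|---|
| 694 | 0.0750 | 0.0749 |
| 701 | 0.0743 | 0.0742 |

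Both meet the target at 701. At 694 the minimum-likelihood interval is just inside it, and Blaker's is at 0.0750 with no room to spare.

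**5. Size of the excess.** Under Clopper-Pearson it is 0.0757 − 0.0750 = 0.0007 at 694. The part due to the dropout step is 0.0757 − 0.0753 = 0.0004.

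**The case against.** The strongest reply is that nothing material depends on this. The 10% is a round planning figure, 771 still yields 701 at a loss of up to 9.1%, and 8 children out of 771 is 1.0%. The worst-case length moves in the fourth decimal place. Baseline sera are taken from every enrolled child (Table 2), so the first and largest survey meets the target with margin. All of this stands, and it limits the point to a correction of the text. It does not make 701, 10% and 771 consistent with one another.

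A reader might go further and infer that the exact interval misses 0.075 even at 701, so that the stated precision is not delivered at all. The document does not support that, for three reasons. It names no construction, and Blaker's and the minimum-likelihood intervals meet 0.075 at 701. Under Clopper-Pearson the value is 0.0753, which is 0.075 at the three decimals the article reports, and it exceeds 0.075 only for true rates near one half. With all 771 measured, the Clopper-Pearson worst case is 0.0717.

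In the other direction, the excess at 694 cannot be put down to rounding if Clopper-Pearson was meant, since 0.0757 rounds to 0.076. Mid-range rates cannot be set aside either: the article gives no expected seroprevalence, and its claim is worded to cover every true rate.

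**Conclusion.** The dropout arithmetic is wrong, whichever interval is used: 771 enrolled with 10% dropout gives about 694 evaluable children, not 701. The consequence for precision is minor and conditional. It appears only at follow-up visits, only if about 10% are lost, only for true rates of about 0.43 to 0.57, and only under an interval such as Clopper-Pearson; there the average length is at most 0.0757 instead of 0.075. At baseline the target is met.

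The check keeps the article's own assumption of a simple random sample, takes the interval as two-sided, and treats the 10% as the fraction of enrolled children missing at a visit. It might be inferred that enrolment must rise to 779, or to 785 (706/0.90 = 784.4, rounded up) for Clopper-Pearson to stay strictly within 0.075. A worst-case excess of 0.0007 in interval length does not justify that, and no conclusion of the study is endangered.

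**What to change.** Keep 771 and replace the sentence with one whose numbers agree, for example: 771 enrolled gives about 694 evaluable children after 10% dropout; the Clopper-Pearson 95% interval then has average length at most 0.076 at any true rate, and at most 0.072 at baseline with all 771.

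The alternative is to keep 0.075, name an exact interval that meets it at 694, and use that interval in the analysis. The minimum-likelihood interval does so; Blaker's sits at the limit, so any loss beyond 10% would take it over.

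Either change costs one sentence. It adds no children and no visits, and in the first version the stated precision becomes less favourable by 0.001.

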With regard to *Aedes*-transmitted infections, DENV is most common in Cambodia and is highly endemic with year-round transmission, peaking from July to November when rainfall is at its highest. Transmission is highly focal but is found in both rural and urban areas in Cambodia [23, 24]. The National Dengue Control Programme (NDCP) has a pediatric hospital-based syndromic surveillance system across the country. At five sentinel sites, clinically suspected cases are sent to Pasteur Institute to confirm DENV infection *via* RT-PCR detection of the virus [20]. Epidemiological studies otherwise rely upon reports of clinically diagnosed dengue-like cases (occasionally confirmed by SD Bioline Dengue Duo rapid tests when available) from hospitalized children under 16 years of age, with little assessment or data in older adults who are less likely to seek care. In Cambodia, average DENV incidence appears to be highest in those under 7 years of age (approximately 41 cases per 1000 person-seasons in one active community-based surveillance study from 2006 to 2008) [24]. Given its reliance on a clinical reporting system, national DENV incidence data likely underestimates true DENV incidence in Cambodia by 3 to 27-fold, per capture-recapture analyses [25]. Among other arboviruses, CHIKV outbreaks are occasionally documented in Cambodia, e.g. one village in Kampong Speu Province experienced a 44% attack rate in 2012 [26]. ZIKV transmission is uncharacterized and may sporadically occur in Cambodia [20].

Considering the vector abundance of *Aedes* mosquitos and the presence of multiple *Aedes*-transmitted viruses in Cambodia, we chose to establish a prospective pediatric cohort using local pagodas (religious temples) for community recruitment and follow-up. This study protocol aims to define the seroprevalence of antibodies to both DENV and *Aedes aegypti* salivary gland homogenate (SGH), describe the epidemiology of symptomatic *Aedes*-transmitted infection in children in this community, characterize the demographic and entomological factors that contribute to DENV infection, and establish the magnitude of human antibody response to *Ae. aegypti* saliva. These data will establish the groundwork on which to better understand the roles of vector-borne determinants of arboviral infection.

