### Community engagement

Engaging community stakeholders is critical to the success of a community-based cohort in Cambodia and is the basis of the effective collaboration between the National Dengue Control Programme, the provincial health departments, and the National Institute of Allergy and Infectious Diseases (NIAID) in conjunction with the Cambodian National Center for Parasitology, Entomology, and Malaria and Control (CNM). Chbar Mon is the largest Ministry of Health operational district in Kampong Speu Province and is the site of the Kampong Speu District Referral hospital, a hospital of approximately 100 beds with 130 staff of medical doctors, nurses and lab technicians. At this hospital, DENV fever is often clinically diagnosed (or sometimes confirmed by a SD Bioline Dengue Duo NS1/IgG/IgM rapid test when available) and reported to the National Dengue Control Programme, but the hospital does not serve as one of the five RT-PCR-confirmed dengue sentinel surveillance sites. Given its proximity to Phnom Penh, samples will be transported to the CNM laboratory for RT-PCR processing.

Four months prior to study start, a community engagement team (including the dengue provincial supervisor) was established and briefed on the overall objectives of the study along with the provincial clinical staff, including three pediatric specialist physicians who see patients in both the private and public sector clinics in Chbar Mon. The community engagement team then met with multiple village chiefs and their villagers across the three easternmost subcommunes of Chbar Mon for information sessions regarding the study. The community engagement team, in conjunction with the village chiefs and local monks, developed a recruitment schedule based on the availability of various community pagodas across Chbar Mon town. An estimated 97% of Cambodians are Buddhist and there are no other major enclaves of other religious groups in Chbar Mon, meaning that the use of pagodas is appropriate to gather a representative sample [28]. To enroll a wide variety of ages and villages within the Chbar Mon town, a different pagoda is designated for recruitment each week during the three-month enrollment period. Cohort enrollment will be structured for four age quadrants: 2–3 years of age, 4–5 years of age, 6–7 years of age, 8–9 years of age with the goal of approximately 192 children in each.

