A central contiguous subarea within the total target area was selected for mosquito trapping. Grid cell centroids were chosen as locations for mosquito traps (roughly 100 m apart, based on *Aedes* flight range) [37]. The site was purposely chosen because of its central location, diversity of ecotypes (an urban area with edges on farms, river and forest), and because historically, community members from this area have had higher numbers of clinical dengue infections. GPS units were then used to select the nearest possible location for setting traps, defaulting to due east of the centroid when necessary. The gravid mosquito trap area covers 0.88 km^2^ of the central township. Collections of adult *Aedes* baited with hay infusions will occur weekly for approximately three months during transmission season but may be adjusted per yield of mosquitos. Community volunteers are trained to maintain and empty *Aedes* traps once per week. Mosquitos are identified by microscopy then stored with desiccant to be brought to the main Phnom Penh laboratory for storage and future molecular analyses.

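### The promised interval length of 0.075 for dengue seroprevalence holds only if children respond independently, which pagoda-by-pagoda recruitment does not secure

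*Protocol article*

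**What the plan says.** Under Sample size calculation, the size is set mainly by dengue virus (DENV) seroprevalence: "With a sample size of 701 accounting for 10% dropout to yield a total goal enrollment of 771 participants". The precision model is "a simple random sample of a binary response (infected or not) with an exact 95% confidence interval on the true proportion", and this interval "will have an average length of less than or equal to 0.075 regardless of the true rate". No design effect, ICC or number of pagodas is given.

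Community engagement describes how children enter. The engagement team, with village chiefs and monks, "developed a recruitment schedule based on the availability of various community pagodas across Chbar Mon town", and "a different pagoda is designated for recruitment each week during the three-month enrollment period". Enrolment is filled to four age bands of about 192 children each. No random draw of pagodas or of children is described.

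Two statements bear on correlation between neighbouring children. Background says "Transmission is highly focal but is found in both rural and urban areas in Cambodia". Mosquito surveillance says of the central trapping subarea that "historically, community members from this area have had higher numbers of clinical dengue infections".

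Statistical analysis reports seroprevalence as a proportion at each timepoint and names no interval method for it. Mixed models and spatial methods appear there for regression and exploratory aims, and quasi-Poisson models for prevalence ratios and rates. None is tied to the interval used in the sample-size statement.

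**The concern.** The length of a binomial interval depends on the number of independent responses. Children reached through the same pagoda are likely to live near one another. If infection is focal, their serostatus will tend to agree, and 701 children then carry less information than 701 independent ones. The article plans to study spatial clustering of disease and IgG response as a scientific question, yet its precision statement allows for none.

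DENV seroprevalence is a primary endpoint, and Table 1 presents it as groundwork for later incidence studies and vector trials. If the stated precision is optimistic, later planning inherits the optimism.

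**Working it through.** **Inputs from the article:** 701 evaluable, 771 enrolled (701 × 1.10 = 771.1), two-sided 95% exact interval, target length 0.075 at any true rate; one pagoda per week for three months.

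**Assumptions, not in the documents:** 12 or 13 pagodas (one per week, no gaps or repeats), equal numbers per pagoda, ICC between 0.005 and 0.05.

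**Step 1: reproduce the stated figure.** The expected length of the exact (Clopper-Pearson) interval is the sum over x of Binomial(x; 701, p) × [upper(x) − lower(x)]. It is largest at p = 0.5, where it is 0.0753. The smallest n with length at most 0.0750 is 706. Blaker's exact interval gives 0.0743 at 701. The stated figure is therefore reproduced under independence, to rounding and choice of exact method.

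**Step 2: allow for correlation within pagodas.**
- Children per pagoda: m = 701/12 = 58.4, or 701/13 = 53.9.
- Design effect: Deff = 1 + (m − 1) × ICC. For 12 pagodas and ICC 0.01: 1 + 57.4 × 0.01 = 1.57.
- Effective sample size: 701/Deff. Same case: 701/1.574 = 445.
- Length: the expected exact length at the effective size and p = 0.5. Same case: 0.0948.

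| ICC (assumed) | Deff, 12 / 13 pagodas | Effective n, 12 / 13 | Length, 12 / 13 |
|---|---|---|---|
| 0.005 | 1.29 / 1.26 | 545 / 554 | 0.0855 / 0.0848 |
| 0.01 | 1.57 / 1.53 | 445 / 458 | 0.0948 / 0.0934 |
| 0.02 | 2.15 / 2.06 | 326 / 341 | 0.1110 / 0.1085 |
| 0.05 | 3.87 / 3.65 | 181 / 192 | 0.1498 / 0.1453 |

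Fewer pagodas would lengthen the interval. With 8, the four lengths are 0.0904, 0.1033, 0.1253 and 0.1765.

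**Step 3: what an unadjusted exact interval would do, if one were reported.** Approximate coverage is 2Φ(0.0753/2 ÷ √(0.25 × Deff/701)) − 1. With 12 pagodas this is about 92%, 89%, 83% and 69% across the four ICCs.

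**Step 4: would more children help?** With k pagodas fixed, the effective size cannot exceed k/ICC. At 12 pagodas and ICC 0.02 the ceiling is 12/0.02 = 600, below the 706 needed, so no number of children restores 0.075. At ICC 0.01 the number needed is 706 × 0.99/(1 − 706 × 0.01/12) = 1698.

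**The case against.** **The pagodas may not act as sampled clusters.** The rotation is meant to spread enrolment over ages and villages, and Study population and site describes a small area. If the pagodas used cover nearly all of it, and inference stops at the town, differences between pagodas largely cease to be sampling error and the widening shrinks. This stands as a limit on size. It does not remove the point: the share of the area's pagodas used is not stated, and Table 1 words the endpoint for children in Kampong Speu. A finite-population correction helps only slightly. With about 4000 local children (assumed), the length is multiplied by 0.908, which offsets a design effect of 1/0.908² = 1.21, or an ICC of about 0.004 with 12 pagodas.

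**Focality is stated for Cambodia in general**, and it concerns transmission rather than cumulative antibody status within one town. This is fair. The remark on the trapping subarea supports variation within the town, but it concerns clinical cases and yields no ICC.

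**A true rate far from 0.5 gives a shorter interval.** At a rate of 0.1 and a design effect of 2 the length is 0.0654. But the promise is made for every true rate.

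**The aim is descriptive.** At ICC 0.01 with 12 pagodas the half-width moves from about 3.8 to 4.7 percentage points, and no decision threshold in the article turns on that.

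A reader might also infer more than the text supports:
- That the reported intervals will certainly undercover. The exact interval appears only in the planning sentence, and the analysis section fixes no interval method.
- That 0.075 was also promised for the saliva endpoint. The sentence concerns infection, and the article says the size was set mainly for DENV.
- That siblings enter together. Sibling enrolment is not described.
- That the age bands show clustering. They are strata.

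**Conclusion.** The point holds as a mismatch within the article between the sampling model behind its precision figure and the recruitment it describes. The length of 0.075 is conditional on independence and is not a property of this design. For any positive correlation within pagodas or villages, with the pagodas regarded as a sample of clusters, the true uncertainty is larger.

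The direction is well supported; the size is not. Under the stated assumptions, the length at a true rate of 0.5 lies between about 0.085 and 0.150, and between about 0.093 and 0.111 for ICCs of 0.01 to 0.02. Near-complete coverage of the target area by the pagodas, with inference limited to the town, would bring it down. A design effect addresses width only. It does not correct any selection bias from scheduling by pagoda availability.

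**What to change.** 1. In Sample size calculation, remove the description of the sample as simple random and the claim that the length holds at any true rate without condition.
2. State the number of pagodas, and give the length as about 0.075 under independence together with a design-effect range. With 12–13 pagodas and a true rate of 0.5, for example, this would be about 0.093–0.095 at an assumed ICC of 0.01 and 0.109–0.111 at 0.02, with both assumptions labelled.
3. Specify a cluster-adjusted interval for primary DENV seroprevalence, with pagoda or village as the cluster: a Korn-Graubard interval, or a cluster-robust interval with degrees of freedom based on the number of clusters. State whether inference is to the town or to the wider province.

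This changes wording and analysis only. Coordinates of participant pagodas and houses are already recorded (Data collection, monitoring, and storage of research samples). The cost is a less favourable stated precision, and with few clusters the adjusted interval is itself less stable.
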